### **5.3 Auditing**

The principal investigator and the SC will provide all the necessary information and material to the participating centres in order to standardize all the protocol-related procedures and to avoid unexpected variability between centres. A preliminary audit between the coordinating centre and the satellite centres will be performed before to start the recruitment phase to offer the major consensus and homogeneity possible. Printed and electronic informative material (complete original protocol, informed consent modules, informative modules for patients and relatives, recruitment check-list, graphic timeline of interventions and visits, order-list for physicians and nurses) will be distributed to every centre.

## **6.0 ETHICS AND DISSEMINATION**

The study will be conducted in line with the protocol, the Declaration of Helsinki (1964) and subsequent amendments and updates (Fortaleza, Brazil, October 2013). Moreover, it is the responsibility of the investigator to ensure that the study will be done in line with to the requirements of Good Clinical Practice(GCP) and the applicable regulatory requirements.

### **6.1 Research ethics approval**

The entire study protocol, including informative material for the patients and modules for the informed consent, will be evaluated by the Local Ethics Committee from the coordinating centre and from all the collaborating centres. The study will not start before obtaining a favourable opinion from the EC, the Competent Authority Authorization and any other authorization required by local regulation. Every intention to modify any element of the original protocol after the first approval will be promptly notified to the Ethics Committee and will be applied only after its written authorization.

Investigator/sponsor will be responsible to submit to the Ethics Committee any amendments to the protocol.

## **6.2 Consent and confidentiality**

Before inclusion in the study, conscious patients must be informed of the purpose and of clinical procedures required by the protocol. The investigators will explain the purpose, risks and benefits associated with study participation. In addition, patients will be informed of his right to withdraw from the study at any time without explanation and without losing the right to future medical care.

If the patient will be unable to comprehend or to give his consent (because of compromised neurological status), the following consent options are acceptable: (i) A priori consent by a legal representative (ii) delayed consent from a legal representative; (iii) Delayed consent from the patient; (iv) waiver of consent; (v) consent provided by an ethics committee or other legal authority. Which options are available at individual participating sites will be determined by the relevant ethics committee and subject to applicable laws. In Italy, the approach to patients unable to provide an informed consent before enrolment will be to consider whether participation is in the best interests of each individual patient and as soon as it is practical and reasonable to do so, to seek the advice of persons interested in the patient's welfare (e.g. family member) to establish that study participation is consistent with the patient's wishes. It is important to know that the randomization does not preclude supportive therapy with IgM preparation but it may only modify the dosage strategies without any expected significant adverse effect for the patient. All participants who recover sufficiently will be given the opportunity to provide informed consent for ongoing study participation and for the use of data collected for the study. Every patient is free to leave the study protocol at any state of the study and can request to retire his consent and, consequently, to ask the elimination of all his data from the database.

In order to comply with legal requirements regarding privacy and the processing of sensitive personal data, Legislative Decree 30/06/2003 n. 196 on the protection of personal data and Regulation (EU) 2016/679 of the European Parliament and of the Council of 27 April 2016 on the protection of natural persons with regard to the processing of personal data and on the free movement of such data, and repealing Directive 95/46/EC (General Data Protection Regulation), each patient will be given an information sheet on the study they participate in and will be asked for sign the consent to the processing of personal data.

Data about personal and private information, included sensible data, will be treated following current legislation on data protection; patients will be identified with a coding system and data registered in anonymous form. Collected data will be processed by the Investigator for the exclusive purposes of fulfil to the present study requirements, and in anonymous form, aggregate in the study database with data obtained from the other patients participating, solely on the basis of finalizing the study and achievement objectives.

Obtained data will not be disclosed except in strictly anonymous and aggregated form. Direct access to the original medical records may be requested only by commissioning DMC of the study and will be accessible by a representative of the CRO, its delegate to perform monitoring on the conduct of the trial, the EC or by the regulatory Authorities, such as personnel of the Italian Ministry of Health and the Italian Medicines Agency (AIFA) to verify that the information entered in the documents of the study are correct and methods that guarantee the privacy and confidentiality of the data are respected. Such verification activities will be always carried out under the supervision of the SC, executed professionally and to guarantee the privacy of the subject.

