#### **1.1.2 Benefits on the use of steroids**

Studies on community-acquired pneumonia show that the excessive production of locally pulmonary cytokines induced by pulmonary infection may cause a severe host inflammatory response inducing pulmonary dysfunction, increasing ICU admission and mortality. Steroids exert potent anti-inflammatory activity by inhibition of leucocytes extravasation, function of macrophages and antigen-presenting cells, production of TNF-alpha, interleukin-1 and nitric oxide. A Chinese report on 201 patients with COVID-19 pneumonia pointed out a survival benefit of more than 15% among patients with ARDS who received Methylprednisolone compared to those who did not.

An interesting report on post-mortem pathological findings in a SARS-CoV-19 patient with ARDS found out interstitial mononuclear inflammatory infiltrates dominated by lymphocytes, in both lungs, implying a severe

immune injury, pulmonary oedema and hyaline membrane formation, finding that suggest a possible role of steroids in this disease' treatment.

Nonetheless, corticosteroid treatment is a double-edged sword and their use remains controversial.

World Health Organization (WHO) recommend against the systematic use of corticosteroids for treatment of viral pneumonia. This recommendation is mainly driven by retrospective observational studies led on SARS, MERS and influenza virus showing no survival benefit and a decelerated viral clearance without affecting the outcome together with the consideration of the many steroid-related possible harms such as secondary infections, gastro-intestinal bleeding and long-terms side-effects.

On the other hand, WHO itself through the Blueprint process has prioritized studies on steroids as an additional therapy that can improve patients' outcome in order to identify actions that can save lives in the immediate aftermath of the COVID-19 pandemic.

Because of methodological limitations in the available evidence, some scientific societies such as Chinese Thoracic Society have developed an expert consensus statement sustaining the use of corticosteroids in 2019-nCoV pneumonia.

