### **1.1.3 Benefits on the use of unfractionated heparin**

Several studies have demonstrated the tight interconnection between thrombosis and inflammation, two processes mutually reinforcing. Both coagulation factors and platelets are directly implicated in the modulation of the host immune response, displaying pro-inflammatory functions independent of their haemostatic effects.

Very recently, a severe derangement in coagulation parameters, showing a pro-thrombotic tendency, has been associated to a poor prognosis in patients affected by COVID-19. Moreover, in the same patients' cohort, the use of Low Molecular Weight Heparin (LMWH) or Unfractionated Heparin (UFH) at prophylactic doses has been demonstrated to be associated with a reduced 28-day in more severe patients with Sepsis Induced Coagulopathy (SIC) score  $\geq 4$  (40.0% vs 64.2%,  $P=0.029$ ), or D-dimer  $> 6$  fold of upper limit of normal (32.8% vs 52.4%,  $P=0.017$ ).

This finding agrees with the already described immune-modulatory properties and protective action of glycocalyx from shedding displayed by heparin.

Despite the biological plausibility, no good evidence is available on the efficacy and safety of heparin on sepsis patients, and many issues have to be addressed, regarding the proper timing, dosages and administration schedules of anticoagulant drugs.

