### **2.3 INTERVENTIONS**

Patients who satisfy all inclusion criteria and no exclusion criteria will be randomly assigned to a LMWH group (Group 1), LMWH+steroids (group 2) or UFH+steroid group (Group 3).

The study is conceived as open-label: the patients and all the health-care personnel will be aware of the assigned group. The treatments will be initiated as soon as possible after randomization (maximum allowed starting time 12h after randomization). In both groups, before enrolment in the study it will be allowed the

administration of low-dosages steroids for ARDS treatment (maximum 320 mg of Methylprednisolone per day for a maximum of 2 days).

**Group 1** (LMWH group): Patients in this group will be administered enoxaparin at standard prophylactic dose (i.e., 4000 UI once day, increased to 6000 UI once day for patients weighting more than 90 kg).

The treatment with enoxaparin will be initiated as soon as possible after randomization (maximum allowed starting time 12h after randomization). The treatment will be administered subcutaneously, daily up to ICU discharge. After ICU discharge it may be continued or interrupted in the destination ward up to clinical judgement of the attending physician.

**Group 2** (LMWH + steroids group): Patients in this group will receive enoxaparin and methylprednisolone.

Enoxaparin will be administered at standard prophylactic dose (i.e., 4000 UI once day, increased to 6000 UI once day for patients weighting more than 90 kg). The treatment will be administered subcutaneously daily up to ICU discharge. After ICU discharge it may be continued or interrupted in the destination ward up to clinical judgement of the attending physician. Methylprednisolone will be administered intravenously with an initial bolus of 0,5 mg/kg followed by administration of 0,5 mg/kg 4 times daily for 7 days, 0,5 mg/kg 3 times daily from day 8 to day 10, 0,5 mg/kg 2 times daily at days 11 and 12 and 0,5 mg/kg once daily at days 13 and 14.

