**Group 3** (UFH + steroid group): Patients in this group will receive unfractionated heparin and methylprednisolone. Unfractionated heparin will be administered intravenously at therapeutic doses. The infusion will be started at an infusion rate of 18 IU/kg/hour and then modified to attain APTT Ratio in the range 1.5-2.0. aPTT will be periodically checked at intervals no longer than 12 hours. The treatment with unfractionated heparin will be administered up to ICU discharge. After ICU discharge anticoagulant therapy may be interrupted or switched to prophylaxis with LMWH in the destination ward up to clinical judgement of the attending physician. Methylprednisolone will be administered intravenously with an initial bolus of 0,5 mg/kg followed by administration of 0,5 mg/kg 4 times daily for 7 days, 0,5 mg/kg 3 times daily from day 8 to day 10, 0,5 mg/kg 2 times daily at days 11 and 12 and 0,5 mg/kg once daily at days 13 and 14. The dosage and time schedule were defined accordingly with dosage used in the large trial on ARDS by Steinberg KP et al (33)

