**Concomitant medications:**

Depending on their clinical status, patients will be treated according to the principles of the Good Clinical Practice and clinical judgement of the attending physician. No other pharmacological therapy or treatment will be influenced from the study protocol. There are no restrictions to concomitant treatments provided to patients in this study. All relevant concomitant medications and treatments taken or administered in the 24 hours before screening and during the study period will be recorded.

Upon clinical judgement of the attending physicians, the patients can receive rescue administration of high- dose steroids or immune-modulatory drugs. Need and timing of rescue treatments administration will be recorded.

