### **2.4.2 Secondary Endpoints:**

- Ventilation free days (VFDs) at day 28, defined as the total number of days that patient is alive and free of ventilation between randomisation and day 28 (censored at hospital discharge). Ventilation is considered as positive pressure ventilation, either invasive or non-invasive. Periods of assisted breathing lasting less than 24 hours for surgical procedures will not count against the ventilation free days calculation;
- Need of rescue administration of high-dose steroids or immune-modulatory drugs;
- Occurrence of switch from non-invasive to invasive mechanical ventilation during ICU-stay;
- Delay from start of non-invasive ventilation to switch to invasive ventilation;
- All-cause mortality at ICU discharge and hospital discharge;
- ICU free days (IFDs) at day 28, defined as the total number of days between ICU discharge and day 28. If death occurs during the ICU stay before day 28 the ICU free days calculation will be 0. The ICU readmission before day 28 after randomization will be considered;
- Occurrence of new infections from randomization to day 28; including infections by Candida, Aspergillus, Adenovirus, Herpes Virus e Citomegalovirus
- Occurrence of new organ dysfunction and grade of dysfunction during ICU stay. Organ dysfunction is defined as a Sequential Organ Failure Assessment (SOFA) score  $\geq 3$  occurring after randomization, grade of dysfunction is measured with SOFA score (see SOFA score in APPENDIX 4) daily from randomization to ICU discharge (censored at day 28);
- Objectively confirmed venous thromboembolism, stroke or myocardial infarction;
- Occurrence of major bleeding (safety end point), defined as transfusion of 2 or more units of packed red blood cells in a day, bleeding that occurs in at least one of the following critical sites [intracranial, intraspinal, intraocular (within the corpus of the eye; thus, a conjunctival bleed is not an intraocular bleed), pericardial, intra-articular, intramuscular with compartment syndrome, or retroperitoneal], bleeding that necessitates surgical intervention and bleeding that is fatal (defined as a bleeding event that was the primary cause of death or contributed directly to death);

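### The consent section says randomisation can only alter IgM dosing and carries no expected significant adverse effect; neither is true of this trial's arms or its own account of risk

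*Protocol*

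**What the plan says.** Section 6.2 of the Protocol lists the consent options for patients who lack capacity and describes the best-interests approach to be used in Italy. It then tells the reader that "the randomization does not preclude supportive therapy with IgM preparation but it may only modify the dosage strategies without any expected significant adverse effect". The next sentence turns to later consent from participants who recover.

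Section 2.3 describes the trial differently. Patients "will be randomly assigned to a LMWH group (Group 1), LMWH+steroids (group 2) or UFH+steroid group (Group 3"). For Group 1, "Patients in this group will be administered enoxaparin at standard prophylactic dose", and Group 2 has the same enoxaparin regimen plus methylprednisolone. For Group 3, "Unfractionated heparin will be administered intravenously at therapeutic doses", again with methylprednisolone. Under concomitant medications the same section adds: "No other pharmacological therapy or treatment will be influenced from the study protocol".

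On risk, section 1.1.2 refers to "the many steroid-related possible harms such as secondary infections, gastro-intestinal bleeding and long-terms side-effects". Section 1.1.3 says that "no good evidence is available on the efficacy and safety of heparin on sepsis patients". Section 2.2.2 excludes patients with active bleeding or at high risk of it. Section 2.4.2 lists "Occurrence of major bleeding (safety end point") and clinically relevant non-major bleeding as safety endpoints, and new infections as a secondary endpoint.

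**The concern.** The sentence makes two claims: what randomisation changes, and how much harm to expect from it. Both appear wrong for this trial.

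Its position gives it weight. In the paragraph on patients who cannot consent, it is the only statement of what randomisation does to the patient and of the harm that may follow. Anyone using that paragraph to judge whether enrolment without prior consent is acceptable finds a reassurance about a treatment that is not under study, and nothing about the treatments that are. What is at stake is the accuracy of the protocol's consent text for a vulnerable group.

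**Working it through.** No published figure needs reproducing and no calculation bears on the point. The check is a comparison of texts.

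**Step 1: is IgM a trial treatment?** Section 2.3 defines three arms from three drugs: enoxaparin, unfractionated heparin and methylprednisolone. No IgM preparation is among them. Elsewhere in the Protocol, IgM appears only as a laboratory titre (section 4.1 and Appendix 4).

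**Step 2: can the claim about what randomisation changes be read so that it is true?** There are two ways to read the reference to dosage strategies.

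| Reading | Compared with | Result |
|---|---|---|
| Randomisation modifies only IgM dosing | 2.3, concomitant medications: the protocol influences no other therapy | Contradicted |
| Randomisation modifies only the dosing of the study drugs | 2.3: Group 1 is assigned no methylprednisolone while Groups 2 and 3 are; Group 3 has a different heparin, given intravenously instead of subcutaneously | Contradicted, because the drugs themselves differ and not only their doses |

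The opening clause, that randomisation does not rule out IgM therapy, is compatible with section 2.3, which places no restriction on concomitant treatment. The rest of the sentence is not.

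**Step 3: is the claim about harm consistent with the rest of the Protocol?**

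| Place | What the Protocol recognises |
|---|---|
| 1.1.2 | Possible steroid harms: secondary infection, gastro-intestinal bleeding, long-term effects; use described as controversial |
| 1.1.3 | Good evidence on heparin safety in sepsis is lacking |
| 2.2.2 | Bleeding risk that contraindicates anticoagulation is an exclusion |
| 2.4.2 | Major bleeding (including intracranial and fatal) and clinically relevant non-major bleeding are safety endpoints; new infections are a secondary endpoint |

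Listing an endpoint does not by itself mean that an excess is expected. Sections 1.1.2 and 1.1.3 go further: one names harms of a randomised drug, and the other says the safety evidence on heparin is not good. A flat statement that no significant adverse effect is expected cannot stand beside them.

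**Step 4: what does the sentence leave out?** Under 1:1:1 allocation of 210 patients (sections 1.3 and 2.6), each arm has 210 / 3 = 70. By design, 2 × 70 = 140 are assigned methylprednisolone and 70 are assigned therapeutic-dose unfractionated heparin. The sentence mentions neither drug. These counts restate the allocation. They do not measure harm from the sentence, nor how many patients enter without prior consent.

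**The case against.** The strongest reply is that nobody reading the whole document could be misled. Under section 6.1 ethics committees assess the entire protocol together with the patient information and consent forms, and that protocol sets out the arms, the steroid harms, the bleeding exclusions and the bleeding endpoints. Section 6.2 also requires investigators to explain risks and benefits, and leaves the choice of consent options to the ethics committee and applicable law. This limits the likely consequence, and that much stands. It does not make the sentence correct. The duty to explain is written for conscious patients, whereas the error sits in the text on those without capacity.

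It is also fair to say that dosage is not wholly beside the point, since heparin intensity does differ between arms. The sentence fails because it refers to IgM, leaves out methylprednisolone and denies significant harm.

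A reader might infer three stronger things that the documents do not support:

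- **That relatives or representatives were given a false account.** The consent material is not available here, and nothing shows that section 6.2 itself is handed to them.
- **That many patients enter by this route because all are ventilated.** Section 2.2.1 admits non-invasive ventilation, and section 6.2 ties incapacity to neurological status. No share is given.
- **That consent would be invalid and data lost from the primary analysis.** The data-removal route in section 6.2 is a request by a patient who withdraws. Nothing links it to this sentence.

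**Conclusion.** The point holds as an internal text error in the consent section. It is not a flaw in the design. The sentence misstates what is randomised, and its assurance about harm conflicts with sections 1.1.2, 1.1.3, 2.2.2 and 2.4.2. It should be corrected because it is the only description of randomisation and its risk in the paragraph governing enrolment without capacity.

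Its size cannot be put as a number of patients, and no effect on the sample size, the primary analysis or the validity of any consent is shown. The conclusion rests on the Protocol text alone and assumes nothing about what the information sheets say. The sentence may have been carried over from another protocol, but the document does not show its origin and the conclusion does not depend on it.

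**What to change.** Delete the sentence from section 6.2. In its place, state what randomisation decides in this trial, namely the type and intensity of heparin and whether protocol methylprednisolone is given, with a reference to section 2.3. Name the harms the Protocol already recognises, at least bleeding and secondary infection, and repeat there that good evidence on heparin safety in sepsis is lacking. Then check the information modules for patients and relatives mentioned in section 5.3, and correct them if they carry the same statement.

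The cost is one paragraph plus ethics committee approval. Section 6.1 allows a change to be applied only after the committee's written authorisation, so notification alone is not enough. No treatment, design element, sample size or analysis changes.

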#### **2.2.2 Exclusion Criteria**

1. Age <18 years
2. On-going treatment with anticoagulant drugs
3. Platelet count < 100.000/mm^3
4. History of heparin-induced thrombocytopenia
5. Allergy to sodium enoxaparine or other LMWH, unfractionated heparin or methylprednisolone;
6. Active bleeding or on-going clinical condition deemed at high risk of bleeding contraindicating anticoagulant treatment
7. Recent (in the last 1 month prior to randomization) brain, spinal or ophthalmic surgery
8. Chronic assumption of oral corticosteroids
9. Pregnancy or breastfeeding or positive pregnancy test. In childbearing age women, before inclusion, a pregnancy test will be performed if not available;
10. Clinical decision to withhold life-sustaining treatment or “too sick to benefit”;
11. Presence of other severe diseases impairing life expectancy (e.g. patients are not expected to survive 28 days given their pre-existing medical condition);
12. Lack or withdrawal of informed consent.

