## **2.4 OUTCOMES**

### **2.4.1 Primary Endpoint:**

- All-cause mortality at day 28.

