## **4.2 STATISTICAL METHODS**

### **4.2.1 Methods for statistical analysis**

All patients enrolled in the study will be entered in the full analysis set independently of his/her treatment time. The intention to treat population will be considered for primary analysis. A descriptive statistical analysis will be performed to describe every relevant variable. In general, categorical data will be presented using counts and percentages, whilst continuous variables will be presented using the number of patients, mean, standard deviation, median, minimum, and maximum. Denominators for calculation of percentages will be taken as the number of non-missing responses in the specified analysis population and treatment group unless otherwise stated, and percentages will be rounded to one decimal. Minima and maxima will usually be reported to the same level of accuracy as the raw data; means, medians and standard deviations will be presented to one further decimal place; standard errors (if presented) will be presented to 2 decimal places more than the raw data. 97.5 % confidence interval will be calculated for primary outcome and for the relevant secondary ones. All data recorded in the CRF will be listed. Distribution of SAPSII and SOFA score (total and for single organ) at admission, P/F ratio distribution at baseline and at day 3, biomarkers PCR, PCT and IL-6 P/F ratio distribution at baseline and at day 3 will be summarized.

The comparison between

1. LMHW + steroids group and LMWH group
2. UHF + steroids group and LMWH group

with binary outcomes will be performed by using Relative Risks (RRs), whereas for continuous data, the difference of means (DMs) will be used. Comparisons involving time to event data will be displayed by using Kaplan-Maier survival curves and summarised by Hazard Ratios (HRs).

All measures of association will be presented with their confidence intervals. A result will be considered as statistically significant if its p-values will be less than 0.025 (2.5%).

The analyses will be performed by using STATA software.

As the study has not been sized to assess the difference between LMHW + steroids group and UHF + steroids group, the results obtained from this comparison will be reported and will be interpreted with caution. The main analyses will not take into account the factors of stratification.

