#### APPENDIX 4: Study timeline

| Time-points                                               |                           | Day-0                                                                                                                                                        | From Day 0 to Say 28 | Day-28 | ICU discharge | Hospital discharge |
|-----------------------------------------------------------|---------------------------|--------------------------------------------------------------------------------------------------------------------------------------------------------------|----------------------|--------|---------------|--------------------|
| Eligibility Screen A                           |                           | X                                                                                                                                                            |                      |        |               |                    |
| Informed consent                                          |                           | X
or as soon as feasible                                                                                                                                  |                      |        |               |                    |
| Allocation                                                |                           | X                                                                                                                                                            |                      |        |               |                    |
| Treatment:                                                | LMWH (group 1)            | 
 
• Enoxaparine from day 0 to ICU discharge
 
                                                                  |                      |        |               |                    |
|                                                           | LMWH + steroids (group 2) | 
 
• Enoxaparine: from day 0 to ICU discharge
 
• Methylprednisolone: from day 0 to day 14
 
             |                      |        |               |                    |

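### Section 6.2 allows all data of a randomised patient to be erased, with no provision to keep arm or day-28 vital status, and is not reconciled with the intention-to-treat primary analysis

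*Protocol*

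**What the plan says.** Four parts of the protocol bear on this point.

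- **Consent may follow randomisation.** The options that section 6.2 accepts for patients unable to consent include "ii) delayed consent from a legal representative; (iii) Delayed consent from the patient; (iv) waiver of consent". Appendix 4 places informed consent at Day 0 "or as soon as feasible".
- **Recovered patients are approached again.** Section 6.2: "All participants who recover sufficiently will be given the opportunity to provide informed consent for ongoing study participation and for the use of data collected".
- **Erasure is open to every patient.** Under section 6.2 a patient may leave at any stage and "can request to retire his consent and, consequently, to ask the elimination of all his data from the database". No exception is made for the allocated arm or vital status.
- **The analysis is to include everyone.** Section 4.2.1: "All patients enrolled in the study will be entered in the full analysis set independently of his/her treatment time". It adds: "The intention to treat population will be considered for primary analysis". The primary endpoint in section 2.4.1 is "All-cause mortality at day 28".

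Section 3.1 makes the trial open-label for patients and staff. Exclusion criterion 12 in section 2.2.2 reads "Lack or withdrawal of informed consent".

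**The concern.** The consent section and the analysis section cannot both be carried out in full if anyone uses the erasure right. An intention-to-treat analysis of 28-day mortality needs the arm and the day-28 status of each randomised patient, and section 6.2 allows both to be deleted.

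The loss would also be linked to the endpoint. A patient who dies without regaining capacity is not asked and cannot request erasure. A patient who recovers is asked, and can refuse the use of data already collected. Where refusals or requests occur, they would therefore take mainly survivors out of the denominator, and observed mortality would rise. Patients know their treatment when they are asked, so willingness to stay in could differ by arm. The between-arm comparison would then be biased, in either direction. Ventilation-free days, ICU-free days, and the thrombotic and bleeding outcomes would lose the same patients.

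This cannot be left wholly to a statistical analysis plan. Such a plan can define populations and sensitivity analyses, but it cannot analyse deleted records.

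**Working it through.** **Inputs.** Section 2.6 gives 210 patients randomised 1:1:1 (70 per arm), control mortality 50%, a 25-point absolute reduction (so 25%), two-sided alpha 2.5% and 80% power. The protocol gives no erasure rate. The share *w* of survivors erased is an assumption, varied below.

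**Step 1: the plan's own figure.** Two proportions, pooled variance, no continuity correction:

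n = [2.2414·√(2·0.375·0.625) + 0.8416·√(0.5·0.5 + 0.25·0.75)]² / 0.25² = (1.5346 + 0.5567)² / 0.0625 ≈ 69.97, so 70 per arm and 210 in total. Power at 70 per arm is 80.0%. The figure is reproduced, and it contains no allowance for lost patients.

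**Step 2: observed mortality after erasure.** If true mortality is *p* and only survivors are erased, observed mortality = p / [p + (1 − p)(1 − w)].

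- One arm, p = 50%, w = 10%: 35 deaths, 3.5 of 35 survivors erased, 35/66.5 = 52.6%.

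**Step 3: equal erasure in both arms.**

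- No true effect, w = 10%: 52.6% in each arm, RR 1, type I error still 2.5%.
- Planned effect (50% against 25%), 70 per arm before erasure:

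| w | Control | Steroid arm | RR | Power |
|---|---|---|---|---|
| 0% | 50.0% | 25.0% | 0.500 | 80.0% |
| 10% | 52.6% | 27.0% | 0.514 | 78.2% |
| 20% | 55.6% | 29.4% | 0.529 | 76.1% |

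**Step 4: unequal erasure, no true effect (50% in both arms).**

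- 15% against 5%: 35/64.75 = 54.1% and 35/68.25 = 51.3%, a false difference of 2.8 points. Type I error is about 3.2% instead of 2.5%.
- 20% against 0%: 35/63 = 55.6% and 35/70 = 50.0%, RR 0.90, type I error 5.6%.

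**Step 5: unequal erasure, planned effect.**

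- Control loses 15% of its 35 survivors, the steroid arm 5% of its 52.5: 35/64.75 − 17.5/67.375 = 54.1% − 26.0% = 28.1 points.
- Control loses 5%, the steroid arm 15%: 35/68.25 − 17.5/62.125 = 51.3% − 28.2% = 23.1 points. Power is about 68%.

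The true difference is 25 points in both cases.

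**Step 6: what a retained count by arm would allow.** Take the 15% against 5% case of step 4, where 5.25 and 1.75 patients are erased on average. Counting them as alive gives 35/70 = 50.0% in both arms. Counting them as dead gives 40.25/70 = 57.5% and 36.75/70 = 52.5%. Such bounds need only the number erased in each arm; if that is deleted too, they cannot be computed.

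**The case against.** The strongest case on the other side has five parts.

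- **The loss is conditional.** Section 6.2 says what a patient may request. If nobody refuses or asks, nothing is lost. This stands. A reader might infer that survivors will leave the mortality analysis and that intention to treat is already broken. The documents do not support that; they show a permitted loss of unknown frequency.
- **Losses need not be survivors only.** A legal representative asked for delayed consent may refuse for a patient who later dies. Conscious patients are to be informed before inclusion, and section 2.2.1 refers to non-invasive as well as invasive ventilation, so the share enrolled without prior consent is unknown. This stands, and it is why the point says mainly survivors.
- **The effect may be small and has no known direction.** Equal erasure produces no false effect under the null and costs little power. The unequal splits are assumed, and reversing them reverses the bias. This stands.
- **Criterion 12 adds little.** A reader might infer that listing withdrawal as an exclusion turns a randomised patient who later withdraws into an ineligible one. Section 2.3 applies the criteria before allocation, Appendix 4 puts the eligibility screen at Day 0, and the criterion orders no deletion. It can be read as consent retracted before randomisation. The wording is loose at most.
- **Withdrawal is an ethical right, and the details may lie elsewhere.** The consent forms and any statistical analysis plan are not at hand. Graded choices could be in the forms, and sensitivity analyses are commonly left to the analysis plan. The right to withdraw is not the fault. But section 6.2 itself states erasure of all data without exception, and section 4.2.1 itself states an analysis of everyone. That conflict is in the protocol and does not depend on what was not seen.

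**Conclusion.** The point holds as a conflict between sections 6.2 and 4.2.1. The protocol allows a randomised patient's whole record, including arm and day-28 status, to be removed after the outcome is largely known and with the allocation known. It does not say how such patients count in the primary analysis.

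The size depends entirely on erasure rates that the protocol does not give. At the assumed rates, mortality is overstated by 2.6 points (10% of survivors erased, 50% mortality), and the between-arm difference shifts by about 2 to 3 points either way (15% against 5%). Larger imbalances would do more: 20% against 0% roughly doubles the type I error. Equal rates leave the null comparison intact. These figures assume that only survivors are erased; refusals on behalf of patients who die would offset part of the inflation.

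This should be fixed, because a deleted primary outcome cannot be recovered afterwards. Loss of unknown frequency does not justify treating it as a fatal flaw.

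**What to change.** 1. In section 6.2, separate three choices: stopping study treatment, stopping further data collection, and objecting to the use of data. State that the first two leave data already collected in the intention-to-treat set.
2. Ask specifically for permission to obtain day-28 vital status from the hospital record.
3. Where ethics or law requires full erasure, keep an anonymised count by arm. Report the primary result with these patients counted as alive and again as dead.
4. Optional: clarify that withdrawal in exclusion criterion 12 means before randomisation.

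The cost is protocol and consent-form wording and one sensitivity table. Ethics committees must agree the wording, and some full erasures may remain. If day-28 status is kept for all 210 patients, the design stays at 70 per arm and 80.0% power under its own assumptions.
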